#### Aerobic exercise prescription

2.5.1

Table 1 provides an overview of the aerobic exercise prescription.

**Table 1 T1:** Aerobic exercise prescription.

Type	Walk
Intensity	Moderate intensity (40%–60% of the heart rate reserve value), calculated according to the results of resting heart rate, maximum heart rate, and distance in the 6MWT, the walking distance is given to the subjects, and the self-perceived exertion method (Borg11–13) is used to monitor the intensity during exercise.For example, in the 6MWT, the resting heart rate is 65 beats/min, the maximum heart rate is 95 beats/min, and the distance is 500 m.Target heart rate: (maximum heart rate-resting heart rate) ∗ 60% + resting heart rate = 83 (±5) beats/min, borg fatigue score is 11–13, 500X60%X5 = 2125. It is recommended that the patient should undergo a 30-min walk of 2125 m.
Time	Walk continuously or intermittently for 40 min.(including 5 min of warm-up, 30 min of exercise, and 5 min of finishing)
Frequency	Five times a week

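### Table 1's worked example gives a walking distance (2125 m) that its own formula does not produce (1500 m), so the prescribed distance cannot be reproduced

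*Protocol article*

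**What the plan says.** Section 2.5 of the protocol article has trained physiotherapists write a personal exercise prescription from each patient's functional assessment. Section 2.5.1, Table 1, gives the aerobic part: walking, 30 minutes of exercise inside a 40-minute session, five times a week. Intensity is set as "Moderate intensity (40%–60% of the heart rate reserve value), calculated according to the results of resting heart rate, maximum heart rate" and the distance in the 6MWT. The walking distance so calculated is given to the patient, and a Borg score of 11–13 monitors effort during the walk.

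The table then works one example. In the 6MWT, "the resting heart rate is 65 beats/min", "the maximum heart rate is 95 beats/min" and "the distance is 500 m". At 60% the target is "resting heart rate = 83 (±5) beats/min". The distance line reads "500X60%X5 = 2125. It is recommended that the patient should undergo a 30-min walk of 2125 m".

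No other section restates or corrects this calculation.

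**The concern.** The distance line does not multiply out, and the example is the only place where the article shows how a 6MWT result becomes a walking target. A physiotherapist who applies the printed formula and one who works back from the printed result would give the same patient different distances.

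This bears on what the study is for. Section 2.7 records how many participants complete the exercise plan, and the Discussion names the completion rate as something this trial must establish for a later randomised trial. If the target distance depends on how the table was read, completing it does not mean the same thing for every participant, and the walking dose delivered is not well defined.

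The tolerance on the heart-rate target also needs checking against the stated intensity range, because the central value already sits at the top of that range.

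**Working it through.** **Inputs, all from Table 1:** resting heart rate 65 and maximum heart rate 95 beats/min in the 6MWT; 6MWT distance 500 m; intensity range 40%–60%; example fraction 60%; multiplier 5; exercise time 30 min; heart-rate tolerance ±5; stated distance 2125 m. The multiplier agrees with 30 min ÷ 6 min = 5.

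**1. Heart-rate target.** (95 − 65) × 0.60 + 65 = 18 + 65 = 83 beats/min. The printed central value reproduces.

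**2. Distance as printed.** 500 × 0.60 × 5 = 1500 m. The printed 2125 m does not reproduce. The difference is 2125 − 1500 = 625 m, and 2125 ÷ 1500 = 1.417, so the stated figure is about 42% higher.

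**3. Can another reading of the table give 2125?**

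| Reading | Distance |
|---|---|
| 40%, 30 min | 500 × 0.40 × 5 = 1000 m |
| 50%, 30 min | 500 × 0.50 × 5 = 1250 m |
| 60%, 30 min | 500 × 0.60 × 5 = 1500 m |
| 60%, 35 min | (500 ÷ 6) × 0.60 × 35 = 1750 m |
| 60%, 40 min (whole session) | (500 ÷ 6) × 0.60 × 40 = 2000 m |
| 85%, 30 min | 500 × 0.85 × 5 = 2125 m |

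No fraction tried within the stated range, and no duration in the table at 60%, gives 2125. Solving for the factor gives 2125 ÷ (500 × 5) = 0.85.

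**4. As pace.** The 6MWT pace is 500 ÷ 6 = 83.3 m/min. The stated walk needs 2125 ÷ 30 = 70.8 m/min, which is 85% of that pace. The formula gives 1500 ÷ 30 = 50.0 m/min, which is 60%.

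**5. Heart-rate band (secondary).** The stated range corresponds to 65 + 0.40 × 30 = 77 up to 65 + 0.60 × 30 = 83 beats/min. The printed band is 83 − 5 = 78 up to 83 + 5 = 88. As fractions of the 65–95 range:

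- 78: (78 − 65) ÷ 30 = 43.3%
- 83: (83 − 65) ÷ 30 = 60.0%
- 88: (88 − 65) ÷ 30 = 76.7%

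The lower half of the band (78–83) is inside 40%–60%. Every value above 83 is outside, by up to 16.7 percentage points.

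**The case against.** **A misprint or a text-reading slip.** This would be the simplest defence, but both sides of the conflict are supported within the table. The 2125 appears as the product and again as the recommended walk. The 60% appears in the distance line and also in the heart-rate formula, where it gives the printed 83. A reader cannot tell which was intended.

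**Other parts of the prescription limit the effect.** This is fair. Type, duration, frequency, the heart-rate formula and the Borg range are all stated. Section 2.8 adds diaries, bracelets, group uploads and weekly calls through which the prescription can be adjusted. A reader might infer that the whole exercise dose is irreproducible; the table does not support that, and only the distance is affected. The monitoring softens the consequence, but it does not define the distance.

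**The ±5 is only a practical tolerance.** This stands in part. The central value is correct and lies within the range. Five beats look large because the example's range is only 30 beats (5 ÷ 30 = 16.7%). The band still runs above the stated ceiling, so the conflict is real but partial, and secondary to the distance error.

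**The maximum heart rate is unspecified.** A reader might add this, because the term heart rate reserve is used. The table does name the source: both heart rates come from the 6MWT. There is no gap to fill here.

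**Conclusion.** The distance line in Table 1 is wrong as written: its terms give 1500 m, while the product and the instruction say 2125 m, which is 42% more. The implied factor of 85% assumes that the 500 m and the multiplier 5 are as intended; the documents do not show which term is in error. The prescribed walking distance therefore cannot be reproduced. The dose delivered and completion of the distance target could vary between participants with the reading of the table. The upper half of the heart-rate band (above 83 and up to 88 beats/min) also exceeds the stated intensity range.

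A reader might go on to infer that adherence, safety and change in 6MWT would all become uninterpretable. The document does not support that. The 6MWT is measured in the same way whatever distance was prescribed (section 2.6.1), and adverse events are recorded with degree, timing, duration and relation to training (section 2.12). What is lost is the link between these results and a defined walking dose. The sample size of 47 and the planned tests are unaffected.

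**What to change.** The sponsor should reconcile four items in Table 1 so that they agree: the percentage factor in the distance formula, the product and recommended distance, the ±5 heart-rate tolerance, and the 40%–60% range. Which value is right is a decision for the clinical team, and this review does not propose one. The corrected example should be re-issued to the prescribing physiotherapists before further prescriptions are written. If participants have already received a prescription, check which factor was used for each.

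The cost is one table correction and a re-issued prescription sheet, plus a short check of existing prescriptions if enrolment has begun.

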### Study intervention

2.5

All subjects will complete all baseline assessments by trained physiotherapists, who work out and demonstrate personalized exercise prescriptions for each patient according to the results of the functional evaluation, including aerobic exercise, resistance training, and flexibility training. Patients will be trained to correctly use self-perceived exertion (Borg) to monitor exercise intensity, distribute family exercise diaries, and exercise bracelets. In addition to dialysis treatment while waiting for kidney transplantation, the family exercise pre-rehabilitation needs to be completed until the patient returns to the hospital for kidney transplantation, and the functional ability, quality of life, and psychological function of all participants will be then re-evaluated. If the participants stop exercising for 1 week or several weeks due to illness, they can participate intermittently and record the disease and intermittent participation in the case report table, which will be explained in the data analysis.

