### Data collection

2.7

In addition to the data collection involving our primary and secondary outcomes, the information regarding patient demographics and clinical variables, such as age, sex, type of occupation, marital status, education, BMI, dialysis of history, and frequency, causes of ESRD, and type of renal replacement therapy, will be also collected. The above-mentioned features are selectively collected on the admission day (baseline), on the day before operation (second follow-up), on the discharge day (third follow-up), and 4 weeks post-operation (fourth follow-up). The proportion of patients who agree to participate in the trial and the reasons for disagreement will be summarized. Moreover, the number and percentage of participants who complete the complete exercise plan will be also recorded. Scheduled data collection at each time point is presented in Table 4.

**Table 4 T4:** Scheduled events and timeline of the trial.

	Study period					
	Time point	Enrollment	Preoperative	perioperative		Follow up
		12+ weeks before surgery	Before surgery or day of surgery	Discharge	1 month	
Enrollment	**Eligibility screening**	×				
	Informed consent	×				
Interventions	ERAS-based home exercise pre-rehabilitation		×			
Assessments	6MWT	×		×	×	×
	Grip strength	×		×	×	×
	4-meter gait speed	×		×	×	×
	5R-STS	×		×	×	×
	Postoperative condition				×	
	SF-36	×		×		×
	HADS	×		×		×

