### Compliance management

2.8

Given a home-based setup, it is important to promote adherence and conduct compliance management. To promote adherence to the program, a self-reported sports diary and a sports bracelet will be given to each participant to provide daily visual feedback and empower responsibility for their daily and weekly goals. Additionally, following a demonstration of the functional resistance exercises at their initial assessment, participants are provided with written and pictorial instructions, as well as a video of all of the exercises. All subjects are pulled into a WeChat group, each exercise record is uploaded to the group, and the “social comparison theory” is adopted to promote patients to complete the exercise.^[22]^ In addition to encouraging patients to complete exercise and punch on time at WeChat Group, the experimenter will conduct weekly telephone surveys to encourage patients to complete family exercise diaries. Any problem can be reported, such as pain or discomfort, to adjust the exercise prescription appropriately. The patients are encouraged during telephone counseling, and their efforts are praised.

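### Table 1's worked walking prescription does not compute: 500 × 60% × 5 is 1500 m, but 2125 m is printed and recommended

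*Protocol article*

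**What the plan says.** Section 2.5.1, Table 1, sets the intensity of the walking component as "Moderate intensity (40%–60% of the heart rate reserve value". It derives this from the resting heart rate, maximum heart rate and distance recorded in the six-minute walk test (6MWT), and adds that "the walking distance is given to the subjects". A distance target is thus part of the prescription.

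The rule is shown only through an example patient, for whom "the resting heart rate is 65 beats/min, the maximum heart rate is 95 beats/min, and the distance is 500 m". Two results follow:

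- a target heart rate, given as "maximum heart rate-resting heart rate) ∗ 60% + resting heart rate = 83 (±5) beats/min", with a Borg score of 11–13;
- a walking distance, given as "500X60%X5 = 2125. It is recommended that the patient should undergo a 30-min walk of 2125 m".

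The same table sets 30 minutes of exercise within a 40-minute session, five times a week. Section 2.5 assigns the individual calculation to trained physiotherapists, "who work out and demonstrate personalized exercise prescriptions for each patient according to the results of the functional evaluation". Section 2.7 states that "the number and percentage of participants who complete the complete exercise plan will be also recorded".

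**The concern.** The formula and its result disagree within one line, and the incorrect result is then repeated as the recommendation. Because the example is the only statement of the distance rule, a physiotherapist has two defensible readings. One is to apply the printed formula; the other is to work back from the printed distance to a larger factor. These give different walking targets for the same patient.

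What is at stake is the definition of the aerobic dose. A feasibility trial meant to prepare a randomised trial should leave a dose that others can reproduce, and this cell does not. There may also be a consequence for the completion measure in section 2.7. If completion were judged against distance, the same walk could count as full completion under one reading and as a shortfall under the other. The article does not say that completion is judged that way, so this is a possibility only.

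**Working it through.** **Inputs, all from Table 1:** resting heart rate 65 beats/min, maximum heart rate 95 beats/min, 6MWT distance 500 m, fraction 60%, multiplier 5, exercise time 30 min. The multiplier is explained by 30 min ÷ 6 min = 5.

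**Step 1. Reproduce the heart rate.** (95 − 65) × 0.60 + 65 = 18 + 65 = 83 beats/min. This agrees with the table, so the 60% is used correctly there.

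**Step 2. Reproduce the distance.** 500 × 0.60 × 5 = 1500 m. The table prints 2125 m, so the figure is not reproduced.

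**Step 3. Look for what would give 2125 m.**

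| Variant | Result |
|---|---|
| 40% × 5 | 1000 m |
| 50% × 5 | 1250 m |
| 60% × 5 (as printed) | 1500 m |
| 70% × 5 | 1750 m |
| 80% × 5 | 2000 m |
| 85% × 5 | 2125 m |
| 60% over 35 min | 500 × 0.60 × 35/6 = 1750 m |
| 60% over 40 min | 500 × 0.60 × 40/6 = 2000 m |
| Heart rate ratio 83/95 applied to 2500 m | 2184 m |

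Of these, only 85% gives the printed figure: 2125 ÷ (500 × 5) = 0.85 exactly. Keeping 60% would require a multiplier of 2125 ÷ 300 = 7.08 (about 42.5 min of walking) or a 6MWT distance of 2125 ÷ 3 = 708 m. Neither fits the rest of the cell.

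**Step 4. Size of the discrepancy for the example patient.**

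- Per session: 2125 − 1500 = 625 m.
- Per week, if the target is unchanged over five sessions: 625 × 5 = 3125 m.
- Ratio: 2125 ÷ 1500 = 1.417, so 2125 m is 42% above 1500 m. In the other direction, 1500 ÷ 2125 = 0.706, so 1500 m is 29% below 2125 m.
- Pace: 500 ÷ 6 = 83.3 m/min in the 6MWT, 2125 ÷ 30 = 70.8 m/min under the printed result, 1500 ÷ 30 = 50.0 m/min under the printed formula.

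If both readings are fixed multipliers of the 6MWT distance, the ratio 0.85 ÷ 0.60 = 1.417 applies to every participant.

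**Step 5. Do the other elements settle the matter?** The target heart rate, the Borg range and the 30-minute duration limit effort and time, but none of them states a distance.

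**The case against.** The strongest reply accepts the arithmetic and disputes its weight.

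- **The dose has other controls.** Trained physiotherapists individualise the prescription, effort is monitored by Borg score with a correctly computed target heart rate, and section 2.8 provides weekly calls in which "Any problem can be reported, such as pain or discomfort, to adjust the exercise prescription appropriately". This stands and limits the practical effect. It does not say which distance a participant should be given at the start.
- **The 40%–60% range refers to heart rate reserve, not to distance.** This also stands. Applying it to distance would give 1000–1500 m, which excludes 2125 m, but the article never states such a distance range. It should not be used to decide which figure is right.
- **The source of the error is unknown.** The 60% may be a misprint for 85%, or 2125 m may be a miscalculation. A wrong 500 or a wrong multiplier cannot be strictly excluded, although the exact 85% fit makes those less likely. The 85% is only the value that reproduces the printed distance, not a documented rule.
- **The effect on completion is hypothetical.** Completion may be judged by sessions, time or the whole programme, including resistance and flexibility work. This stands; the contrast in which a 1500 m walk is 100% of one target and 71% of the other holds only if distance is the criterion.
- **The weekly total assumes no adjustment.** This is correct. The firm figure is 625 m per session for the example patient.

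An error in reading the PDF is an unlikely explanation, since 2125 appears twice and the adjoining heart rate calculation came through intact.

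**Conclusion.** The concern holds, and the example is wrong as written. The printed formula gives 1500 m, the printed result is 2125 m, and nothing elsewhere in the article corrects or explains the difference. The prescribed walking distance is ambiguous by a factor of 1.42, or 625 m per session for the example patient.

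This rests on arithmetic within one table cell and needs no outside assumption. Extending the factor to other participants assumes a constant multiplier; the weekly figure assumes five unadjusted sessions. The article does not show that any patient received a wrong dose. It should be fixed because it is the only statement of the distance rule.

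**What to change.** Correct the Table 1 cell to one of two consistent versions:

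- **(a)** 60% with 500 × 0.60 × 5 = 1500 m; or
- **(b)** 85% with 500 × 0.85 × 5 = 2125 m, with a sentence explaining why the distance factor differs from the 60% used for the heart rate target.

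The choice belongs to the sponsor's clinicians, because the article does not show which was intended. If prescriptions have already been issued, compare them with the corrected cell and note any that used the other figure.

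It would also help, though it is not essential to the correction, to record the factor and distance given to each participant in the case report form if these are not already captured. The cost is one table cell, a short check of any issued prescriptions and, at most, two form fields.

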This Phase I trial is essential to understand potential recruitment rates, dropout rates, patients who receive transplants or die during the study, and the completion rate of this program to accurately motivate participants for future RCTs.

Collectively, this trial is a practical, single-center, single-arm, exploratory clinical trial. We plan to show that ERAS-based home exercise pre-rehabilitation will reduce the adverse effects of frailty, cardiopulmonary dysfunction, and psychological dysfunction on the prognosis of renal transplantation.

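### Table 1's only worked walking prescription contradicts itself: 500 × 60% × 5 is 1500 m, but the table recommends 2125 m, which needs a factor of 85%

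*Protocol article*

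**What the plan says.** Section 2.5 has trained physiotherapists "who work out and demonstrate personalized exercise prescriptions for each patient according to the results of the functional evaluation". Table 1 in section 2.5.1 sets out the aerobic part. The stated intensity is "Moderate intensity (40%–60% of the heart rate reserve value"), and the table says that "the walking distance is given to the subjects, and the self-perceived exertion method (Borg11–13) is used to monitor the intensity during exercise".

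The table then works one example: resting heart rate 65 beats/min, maximum heart rate 95 beats/min and 500 m walked in the 6MWT. It applies 60% of the heart rate reserve and arrives at "resting heart rate = 83 (±5) beats/min, borg fatigue score is 11–13". It goes on to the distance: "500X60%X5 = 2125. It is recommended that the patient should undergo a 30-min walk of 2125 m". The session has 30 minutes of exercise between a 5-minute warm-up and a 5-minute finish, five times a week.

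The article contains no other distance formula and no second example.

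**The concern.** The equation in the distance line is false as printed, and its result is carried into the recommendation. This is the only published instruction for turning a 6MWT distance into a walking target, so a reader cannot settle from the article which number was meant.

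Three things are at stake:

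- **The intervention as delivered.** Staff who apply the formula would give the example patient 1500 m. Staff who copy the result, or infer 85% from it, would give 2125 m.
- **Reproducibility.** The trial is meant to prepare a larger randomised trial and possibly yield an application protocol. A walking target that cannot be reproduced from its own example works against that.
- **Completion, conditionally.** Section 2.7 says that "the number and percentage of participants who complete the complete exercise plan will be also recorded", and the Discussion wants "the completion rate of this program to accurately motivate participants for future RCTs". If completion were judged against the prescribed distance, it would depend on the factor used. The article does not define completion by distance, so this is a possible consequence and not a demonstrated one.

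**Working it through.** **Inputs, all from Table 1:** resting heart rate 65, maximum heart rate 95, 6MWT distance 500 m, fraction 60%, multiplier 5, five sessions a week. I read the multiplier as 30 min / 6 min = 5, which matches the 30 minutes of exercise.

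**Step 1: the heart rate line.** (95 − 65) × 0.60 + 65 = 18 + 65 = 83 beats/min. This reproduces the printed target, so 60% is used correctly here.

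**Step 2: the distance line.** 500 × 0.60 × 5 = 1500 m. The printed 2125 m does not reproduce.

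**Step 3: which factor gives 2125 m?** 500 × 5 = 2500 m, and 2125 / 2500 = 0.85 exactly.

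| Factor or variant | Distance |
|---|---|
| 40% | 1000 m |
| 50% | 1250 m |
| 60% (as printed) | 1500 m |
| 70% | 1750 m |
| 80% | 2000 m |
| 85% | 2125 m |
| 100% (6MWT pace) | 2500 m |
| 60% over the whole 40 min (500 × 0.60 × 40/6) | 2000 m |
| Target over maximum heart rate, 83/95 = 87.4% | 2184 m |

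Of the variants tried, only 85% returns the printed figure.

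**Step 4: can the ±5 beats/min explain it?** The article never converts beats to metres, so this assumes that one percentage applies to both lines. The upper end, 83 + 5 = 88 beats/min, is (88 − 65) / 30 = 76.7% of the reserve. In the distance formula that gives 2500 × 0.767 = 1917 m, still below 2125 m.

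**Step 5: size of the gap.**

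- Per session: 2125 − 1500 = 625 m, and 625 / 1500 = 41.7%.
- Per week: 625 × 5 = 3125 m.
- Pace: 500 / 6 = 83.3 m/min in the 6MWT, 1500 / 30 = 50.0 m/min by the formula, and 2125 / 30 = 70.8 m/min by the printed result.

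The metre figures belong to this example. The 41.7% holds for any patient if 85% is used in place of 60%, since 0.85 / 0.60 = 1.417.

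**The case against.** The strongest reply is that the recommended distance may be exactly what was intended. The figure 2125 is exact at 85% and is printed twice, as the result and as the recommendation, so the printed 60% may be the misprint. On that reading no patient is given a wrong distance. This stands as a possibility, and it is why the finding is a contradiction between factor and result and not a claim that 2125 m is too far. It does not remove the contradiction, because the article contains nothing that lets a reader choose.

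A related reply is that the declared 40%–60% refers to heart rate reserve, not to walking distance. This also stands. The 1000–1500 m that the formula gives at 40%–60% is a limit only if the table means the same percentage in both lines, as it prints. The false product in step 2 does not depend on that.

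Third, a 42% difference in distance is not a 42% difference in total dose. Duration, frequency, target heart rate and Borg range are the same under either reading, prescriptions are individual, and section 2.8 offers a route for correction: "Any problem can be reported, such as pain or discomfort, to adjust the exercise prescription appropriately". This is fair. What differs is the distance target and hence the pace, and the safeguards limit the harm. They do not tell the physiotherapist which distance to write down.

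**Conclusion.** The concern holds. Table 1's printed formula gives 1500 m and its printed recommendation is 2125 m, a difference of 625 m per session or 41.7%. The recommendation would need a factor of 85%, which is not stated anywhere in the article.

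This follows from the table's own inputs by direct arithmetic. The only reading added is that the multiplier 5 stands for five 6-minute blocks, and the false product does not depend even on that. Which of the two numbers is wrong cannot be determined from the document. That staff would in fact diverge is a risk, not something the document shows.

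Severity is minor: the error lies in the intervention's instructions and leaves the sample size, the outcome definitions and the planned tests untouched.

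**What to change.** Correct the cell so that factor and result agree, in one of two ways:

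- If 60% is intended, print 500 × 60% × 5 = 1500 m and recommend a 30-minute walk of 1500 m.
- If 85% of the 6MWT pace is intended, print 500 × 85% × 5 = 2125 m and state that this distance factor is separate from the 40%–60% of heart rate reserve.

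Tell the physiotherapists before enrolment which factor applies. In the same edit it would help to say whether the ±5 beats/min is a measurement tolerance around the target; the finding does not depend on that.

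The cost is one table cell and one line of instruction. No extra data or patients are needed.
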